##### Phage Kinetics

To evaluate the local phage titer during phage therapy, the draining fluid of MSI patients and nasal swabs from CRS patients will be collected. To evaluate the systemic exposure of phages, phage titration will be performed on the collected serum samples. In all blood samples, phage quantification will be performed using the double agar overlay method (viable fraction) and qPCR (total titer in the blood). Viable phages will be isolated and their whole genome sequenced to identify possible mutations (see Translational research). Serum samples taken from sepsis patients will help elucidate how long phages remain detectable in the blood before the next intravenous administration. This information will be crucial to evaluate the currently used application protocol. Furthermore, based on hemoculture results, we will evaluate phage persistence after cessation of therapy, in the presence or absence of their bacterial host. The bacterial load in the blood will be quantified by determining and extrapolating ‘time-to-positivity’ (TTP) of the hemocultures. The TTP is defined as the time from the start of incubation to a positive signal.

The clearance of phages by the immune system may affect the efficacy of phage therapy [11]. Low titers of phage-specific antibodies are common in patients because phages are encountered on a daily basis, but titers may increase during phage therapy. The induction of the innate immune system (clearing phages through phagocytosis (i.e., the reticuloendothelial) system) as well as the adaptive immune system (production of phage-neutralizing antibodies), has been associated with early depletion of phages and subsequent impairment of efficacy [12,13]. It may be necessary to compensate for this phenomenon by repeating phage administration, increasing phage titer, using different phages or a phage cocktail. Therefore, from all patients who are treated with phage therapy, serum samples will be processed using the phage neutralization assay, as previously described [8], to detect antiphage antibodies on the time points listed in Table S1.

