#### 2.4.2. Treatment-Specific Parameters: Phage Treatment Group

If all eligibility criteria are met and a positive phagogram is obtained, the patient will be included in the phage treatment group. The CBL will design the treatment protocol and document it in the CBL final treatment plan, which is also registered in the patient’s medical file. Phages will be administered locally, through a draining system for MSI patients (as previously described [8]), intranasal for CRS patients and intravenously for sepsis patients. The phages that will be used are produced according to a monograph at the QAMH [7]. Furthermore, these phages are well-characterized, in that the genetic sequence and therefore the confirmation of each phage’s strictly lytic profile and absence of undesired genetic determinants (e.g., toxins and antibiotic-resistance genes) are available. These analyses are verified independently by Sciensano, the Belgian federal research institute for public health, and summarized in a so-called genetic passport. Moreover, each batch of phages (phage stock) produced at the QAMH is quality controlled by Sciensano before it can be used in humans [7,8]. Furthermore, phage stock titers will be determined frequently and prior to each dilution for phage therapy. For each individual phage that will be used, stability tests of the diluted preparations will also be performed for the different indications. In this way, we know how frequently we need to prepare new diluted preparations during the treatment to maintain a therapeutic target titer.

Improvements in pharmacological insights during phage therapy development is critical, particularly towards obtaining a better understanding of treatment failures [9]. As it is likely that the systemic exposure of a virulent phage is significantly modified due to its adsorption to the susceptible bacterial cells causing the infection, it becomes difficult to extrapolate the systemic exposure of other antimicrobial drugs to that of the phages. Furthermore, virulent phages multiply within their host and, as a result, while classic antibiotics decay over time, bacteriophage titers increase in the presence of a susceptible host [10]. Multiple samples will be taken (as detailed in Table S1) to monitor the patient and treatment progress. These samples will also be used to gain insight into the physiology of the phages during phage therapy, as detailed below.

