To assess the potential of phage therapy with respect to infection eradication, a combination of quantitative and qualitative outcome measures will be evaluated. As stated above, blood laboratory test results and clinical parameters will be collected to monitor the evaluation of the patient’s health status during treatment. The bacterial load during and after phage therapy will be measured. Several bacterial cultures will be taken from all patients. For CRS patients this entails nasal swabs, for sepsis patients this includes hemocultures. In case of MSI, it is not feasible to have multiple deep tissue cultures taken after the wound has been closed. As an alternative, during phage therapy, fluid collected in the draining system that is used for the application of phage therapy will be cultured. As these draining tubes are typically removed at the end of phage therapy, cultures can no longer be obtained during the follow-up period, unless there is a need for revision surgery (i.e., in case of recurrence of infection). Therefore, the main outcome measure for MSI patients is a disease-free period of at least one year after cessation of therapy. The bacteria and phages that are isolated from the various samples described above and listed in Table S1, will be stored for further analysis at −80 °C and 4 °C, respectively (see Section 2.5. Translational Research).

For CRS patients, specific clinical and quantitative outcome measures are available. These include endoscopic (Modified Davos, Lund–Kennedy), radiological (Lund–Mackay) and combined (European Position Paper on Rhinosinusitis and Nasal Polyps (EPOS) criteria for controlled or uncontrolled CRS) scoring systems, which will be collected and compared before, during and after phage therapy. Moreover, to evaluate the olfactory function in CRS patients, smell tests (Sniffin’ Stick test) will be carried out before and after phage therapy. For sepsis patients, the SOFA score will be recorded before, during and after treatment. The SOFA score is an internationally used score to objectively determine the degree of multiple organ failure in critically ill patients. A (rapid) decrease of the SOFA score (delta SOFA) is associated with a better survival and vice versa. Delta SOFA is defined as the difference between the SOFA score at baseline (prior to phage therapy) and the SOFA score at the final day of phage therapy.

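### On-therapy bacterial load is used as efficacy evidence although the cultured specimens may contain active phage, so killing after sampling may be read as a fall in the patient's load

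*Protocol article*

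**What the plan says.** The Assessment of Efficacy text in section 2.4.2 (under Phage Dynamics) opens with its purpose: "To assess the potential of phage therapy with respect to infection eradication, a combination of quantitative and qualitative outcome measures will be evaluated". Among those measures, "The bacterial load during and after phage therapy will be measured". The specimens are then named. "For CRS patients this entails nasal swabs, for sepsis patients this includes hemocultures". For MSI, where repeated deep tissue cultures are not feasible once the wound is closed, "fluid collected in the draining system that is used for the application of phage therapy will be cultured".

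The routes of administration stand earlier in section 2.4.2: "Phages will be administered locally, through a draining system for MSI patients", "intranasal for CRS patients and intravenously for sepsis patients". The specimens cultured on therapy are thus taken from the drain, the nose and the blood into which phage is given.

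The Phage Kinetics text adds the method for sepsis: "The bacterial load in the blood will be quantified by determining and extrapolating" hemoculture time-to-positivity (TTP), counted from the start of incubation to the positive signal. The same text plans phage titration of drain fluid, nasal swabs and serum. In blood it separates the viable fraction (double agar overlay) from the total (qPCR).

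Two further statements bear on the point. Section 2.4.1 admits a patient to the phage group only if every isolated species is susceptible to the available phages. Section 2.4.2 says that "bacteriophage titers increase in the presence of a susceptible host".

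**The concern.** Reading a bacterial load from a culture assumes that growth in the bottle or on the plate reflects only the number of viable organisms present when the sample was taken. A lytic phage carried over in the specimen can break that assumption. It was selected for activity against this patient's isolate, and by the protocol's own account it multiplies when a susceptible host is present. If it goes on killing after the sample has left the patient, growth is delayed or absent for a reason unrelated to what happened in the patient.

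Controls receive no phage, so this mechanism cannot act in them. Section 2.6 presents summaries by treatment received. Any such error would therefore appear only in the phage group, and only as better microbiological results. At stake is whether a longer TTP or a negative on-therapy culture can be cited as evidence of eradication.

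**Working it through.** The protocol states no figure on this point and gives no power calculation, so there is nothing to reproduce. The check has two parts.

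**1. The statements side by side**

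| Indication | Phage given | Cultured on therapy | Phage titrated in |
|---|---|---|---|
| MSI | through the drain | drain fluid | drain fluid |
| CRS | intranasally | nasal swab | nasal swab |
| Sepsis | intravenously | hemoculture, load from TTP | serum |

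In MSI and CRS the same specimen type is both cultured and titrated for phage. In sepsis both come from blood. The protocol therefore expects that phage may be present. The article does not link the two results: it states no rule for reading a culture in the light of the phage titer, and attaches no condition about phage to the TTP extrapolation.

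**2. How a kill in the bottle is read back**

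Inputs, none of them in the documents and all assumed: kill fraction after sampling *f* from 0 to 0.999; doubling time *Td* from 20 to 60 minutes; expected viable organisms per bottle *n0* of 10 or 100. The model takes exponential growth from *N0* organisms to a detection threshold *Nd*, with one kill of fraction *f* and normal growth of the survivors.

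- Without phage: TTP = Td × log2(Nd/N0).
- With phage: N0 becomes N0 × (1 − f), so TTP lengthens by Td × log2(1/(1 − f)).
- Extrapolating back from the longer TTP returns N0 × (1 − f), an apparent fall of log10(1/(1 − f)). *Td* and *Nd* cancel.

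Example: f = 0.9 and Td = 20 min give (20/60) × log2(10) = 0.333 × 3.32 = 1.11 h, read as log10(10) = 1.0 log10.

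| f | TTP shift, Td 20 min | TTP shift, Td 60 min | Apparent fall in load |
|---|---|---|---|
| 0 | 0 h | 0 h | 0 log10 |
| 0.5 | 0.33 h | 1.00 h | 0.3 log10 |
| 0.9 | 1.11 h | 3.32 h | 1.0 log10 |
| 0.99 | 2.21 h | 6.64 h | 2.0 log10 |
| 0.999 | 3.32 h | 9.97 h | 3.0 log10 |

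The last column restates *f* on the log scale. It shows that the method offers no protection against a kill after sampling; it does not show that such a kill occurs.

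Growth can also be abolished. With a Poisson count, P(no survivor) = exp(−n0 × (1 − f)):

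- n0 = 10: f = 0.9 gives exp(−1) = 0.37; f = 0.99 gives exp(−0.1) = 0.90.
- n0 = 100: f = 0.9 gives exp(−10), about 0; f = 0.99 gives exp(−1) = 0.37.

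**The case against.** A reader might infer that phage carry-over is bound to be counted as efficacy, that a 10- to 1000-fold spurious fall should be expected, and that nothing in the design would expose it. The documents support none of these.

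- **Certainty.** No section gives the phage titer at sampling, the interval from dose to sample, or a kill fraction. The remark about rising titers contrasts phage with antibiotics in the body; it is not a statement about culture bottles. How long phage stays detectable in blood between doses is a question the study sets out to answer.
- **Size.** A 10- to 1000-fold fall is an assumed kill of 1 to 3 log10 restated. Zero belongs in the range.
- **Detection.** Phage titration of drain fluid, swabs and serum is planned, with a viable fraction in blood. Section 2.5.1 retests isolates recovered during and after treatment against the applied phages. These data can flag affected samples.
- **Weight.** Bacterial load is one of several measures in a registry that section 2.6 calls mainly descriptive and exploratory. The main MSI outcome is at least one disease-free year, adopted because cultures end with drain removal. SOFA and the CRS endoscopic, radiological and patient-reported scores do not depend on culture.
- **Unseen material.** Sampling times are in Table S1, and laboratory handling may be in the full protocol. Silence in the article does not show that no safeguard exists.

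All of this stands, and it limits the point. It does not remove it: the article does place on-therapy load under efficacy, does take it from specimens likely to hold phage, and does extrapolate TTP to load without condition. The availability of phage titers helps only if they are used when the cultures are interpreted.

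**Conclusion.** The point holds in limited form. On-therapy bacterial load, as the article defines it, may be biased by phage killing after sampling in all three indications. This mechanism can act only in the phage group and only in its favour. The size cannot be stated: it equals the kill fraction in the specimen, from zero upward. The hours and log10 values above rest on assumed kill fractions, doubling times and organism counts, and on a single-kill model.

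The concern is mainly with cultures taken during therapy and weakens afterwards as phage clears. It does not touch the MSI disease-free outcome, SOFA or the CRS clinical scores. What it changes is whether an on-therapy negative culture or longer TTP can be cited as eradication.

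**What to change.** 1. Report every on-therapy culture from drain fluid, nasal swab or blood beside the viable-phage titer already planned, and label it as phage present where viable phage is detected. In sepsis, use the serum titer that belongs to the same draw, if the sampling schedule provides one. The viable count is the relevant one, not the qPCR total.
2. For samples so labelled, do not convert TTP to bacterial load unless removal or neutralisation of phage before culture is documented. If the laboratory already does this, one sentence saying so settles the matter for those samples.
3. Rest any claim of microbiological eradication on samples without detectable viable phage.
4. Keep the clinical outcomes (MSI disease-free year, SOFA, CRS scores) as the main efficacy evidence.

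The cost is in wording and in data yield; no extra sampling and no change to treatment is needed. Fewer on-therapy samples will give a load estimate. Microbiological efficacy evidence in MSI becomes sparse, because drains are typically removed when therapy ends and later cultures arise only at revision surgery. Removing all on-therapy cultures from the efficacy summary would go further, but would leave MSI almost no microbiological data. That is a trade-off for the sponsor and is not required here.

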#### 2.4.3. Follow-Up Parameters: Phage Treatment Group

Patients who were treated with phage therapy will follow the standard-of-care for phage therapy until three months after the final administration of phage therapy. After these three months, they will follow the standard-of-care follow-up schedules for the underlying infection, confer patients in the control group. Data will be collected until one year after the final phage administration.

#### 2.4.4. Treatment-Specific and Follow-Up Parameters: Control/Standard Treatment Group

The CBL will also set up the treatment protocol for control patients (standard, non-curative treatment). Control patients will only be subjected to blood analyses and sampling when required according to the standard-of-care for the underlying pathology. The results of all blood and culture tests that are performed in that period with respect to the underlying infection will be recorded in the patient registry. All bacteria isolated from the infected site will be stored for further analysis. All eligible MSI and CRS patients will also be asked to fill out PROMIS (for MSI and CRS) and SNOT-22 and VAS (CRS) questionnaires at standard follow-up outpatient visits. Patients will be followed, and the data will be collected until one year after the CBL’s final treatment plan.

### 2.5. Translational Research

#### 2.5.1. Microbiological Analysis of Patient Bacterial Isolates and Identification of Novel or Long-Circulating Phage Mutants

When different phages are available for treatment (based on the phagogram), phage compatibility will be assessed by investigating the interaction between phages inside the cocktail. The synergy between phages can be investigated, as described by Schmerer [14]. When phages are not available (based on a negative phagogram), the patient will be included in the control group, but the patient’s bacterial isolates can be used to isolate additional phages (e.g., from hospital sewage) to extend the phage bank for future patients. Alternatively, these phage-resistant bacteria can also be used to train phages to broaden their bacterial host range, which is valuable in order to comprise the full diversity of the pathogens and to surpass bacterial-resistance development [15]. The creation of such host range mutants will be performed according to a modified Appelmans’ protocol [16].

All bacterial isolates taken during and after phage treatment will be tested for sensitivity against the applied phages and the efficiency of plating (EOP) will be compared to the initial (pre-treatment) one. The EOP is defined as the number of plaques a phage is able to produce when incubated with a bacterial strain relative to the number of plaques the phage is able to produce when incubated with its host or reference bacterial strain. Antibiograms will be compared to the baseline antibiogram to determine if the susceptibility to antibiotics has changed and look for synergistic interactions [17]. Furthermore, bacterial isolates will be fully characterized by whole genome sequencing, using a combination of Illumina and Nanopore sequencing [18] to obtain optimal genome assemblies. This will be crucial to improve the functional annotation of the genomes. We will focus on the annotation of elements that could be directly linked to lytic phage efficacy. Genome features, such as plasmids, CRISPR–Cas systems, prophages, restriction–modification (R-M) systems and receptors are all linked to susceptibility [19].

During and after phage treatment, phage mutants that have naturally evolved to be more efficient in the patient environment, could also arise. Therefore, phage isolation from patient samples will be performed during and after treatment. These ‘in patient-optimized’ phages will then be characterized by whole genome sequencing and will be the basis for next-generation therapeutic phages that could be used in personalized phage therapy.

#### 2.5.2. Characterization of the Phage Library and Using Machine Learning to Predict Host Range Phenotype from the Genotype

By expanding our dataset with the clinical data from this study and in vivo-occurring resistance mechanisms, we aim to develop predictive models of phage infectivity. These models will enable us to set up a decision tool to improve phage cocktail design and further fundamental insights into the determinants of phage infectivity. As previously mentioned, available phages will be tested for phage infectivity on each bacterial isolate (before treatment). These data will not only be used to identify the phages for treatment, but also to enhance our dataset for the machine learning approaches to predict phage infectivity based on whole genome data. We want to capitalize on the large amounts of sequencing data that will be used to train a decision algorithm to better predict infectivity towards a new bacterial host. As the number of genomics features that could be employed is vast, feature selection will be performed based on the presence of genetic systems linked to phage susceptibility, including prophages, CRISPR–Cas systems, R-M or known genes coding for membrane receptors.

### 2.6. Statistical Analysis

As the aim of this registry is mainly descriptive and exploratory, patient characteristics and outcomes recorded at standard-of-care scheduled follow-up assessments will be presented using simple summary statistics.

Categorical variables will be summarized using the frequency and percentage for each category. Continuous variables will be summarized using the mean, standard deviation, inter-quartile range and minimum and maximum values. These summary statistics will in addition be presented according to the clinically relevant categories; i.e., according to the treatment received.

Complications will be reported both at the patient and the AE level. Given the exploratory nature of this study, any results will have to be interpreted carefully.

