### 2.2. Study Design

This is a prospective, monocentric and observational registry. In consultation with the hospital’s Ethics Committee, phage therapy is considered to be standard-of-care only in patients with difficult-to-treat infections for whom curative treatment alternatives (antibiotic and/or surgical) are not available (‘last-resort cases’). Whether the patient will receive phage therapy (phage treatment group) or a standardized non-curative (e.g., amputation, chronic antibiotic suppression) treatment (control group) depends solely on the susceptibility of the causative pathogen(s) against the available phages. More specifically, in case active phages are not available against all causative pathogen(s), the patient will not undergo phage therapy.

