#### 2.3.1. Sample Size Calculation

Since data on the application of phage therapy for MSI, CRS and sepsis are currently scarce, we are unable to perform a power analysis due to the absence of an objective effect size. The main aim of this registry is to obtain safety and efficacy data. Based on previously received requests for phage therapy, an estimated 150 patients will be included. Furthermore, within this patient population, approximately 75 will have a positive phagogram and can therefore be treated with phage therapy.

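### The MSI main outcome is a one-year disease-free period, but Section 2.6 offers only frequencies and percentages, so the reported rate depends on how deaths and losses are counted

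*Protocol article*

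**What the plan says.** **Method.** Section 2.6 states that outcomes at scheduled follow-up "will be presented using simple summary statistics". It adds: "Categorical variables will be summarized using the frequency and percentage for each category". Summaries are also "presented according to the clinically relevant categories; i.e., according to the treatment received". It names no other method for outcomes and calls the registry mainly descriptive and exploratory.

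**MSI outcome.** Under Assessment of Efficacy (Section 2.4.2), "the main outcome measure for MSI patients is a disease-free period of at least one year after cessation of therapy".

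**Follow-up.** For phage-treated patients (Section 2.4.3): "Data will be collected until one year after the final phage administration". For controls (Section 2.4.4), "data will be collected until one year after the CBL" group's final treatment plan is made, which is a different starting point.

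**Control treatment.** Section 2.2 describes it as "standardized non-curative (e.g., amputation, chronic antibiotic suppression) treatment (control group").

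**Size.** Section 2.3.1 says "an estimated 150 patients will be included", of whom about 75 are expected to receive phages, across all three indications. The MSI share is not given.

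**The concern.** The MSI outcome is a duration with a fixed horizon, and the stated method turns it into a yes/no count. In the phage group the required disease-free window fills the whole of the follow-up after the last phage dose, so there is no slack. A patient last seen infection-free at eight months is neither a success nor a failure, and a percentage has no place for that partial information.

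Controls are harder to place. Their data stop one year after the treatment plan, while the outcome clock starts when therapy stops. A control whose therapy ends after the plan cannot be observed for a full year from cessation. Under chronic suppression, cessation may never come.

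These are last-resort patients whose infection the Introduction describes as advanced, so some deaths and losses are plausible. What is at stake is the registry's main efficacy figure for MSI, which the Conclusions hope will support later clinical studies. Analysts who follow the text faithfully could report materially different rates from the same data.

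**Working it through.** The article gives no event rate, loss rate, power or effect size, so it has no figure to reproduce. The rates below are assumptions chosen to show a range.

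**Inputs.** One-year risk of recurrence 30%; death and loss each 5%, 10% or 15%. Each is the risk if that cause acted alone, with constant and independent hazards.

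**Formulas.** For each cause, λ = −ln(1 − risk). Write λr, λd and λl for recurrence, death and loss, and Λ for their sum.

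- Observed disease-free at one year, out of all included: F = exp(−Λ)
- Observed recurrences: R = (λr/Λ)(1 − F)
- Percentage among those with known infection status: F/(F + R)
- Target A, alive and recurrence-free: exp(−(λr + λd))
- Target B, one minus the cumulative incidence of recurrence: 1 − [λr/(λr + λd)] × [1 − exp(−(λr + λd))]

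**Worked case, 30/15/15.** λr = 0.357 and λd = λl = 0.163, so Λ = 0.682.

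- F = 0.70 × 0.85 × 0.85 = 50.6%
- R = (0.357/0.682) × 0.494 = 25.9%
- Known status = 50.6/(50.6 + 25.9) = 66.2%
- Target A = 0.70 × 0.85 = 59.5%
- Target B = 1 − (0.357/0.519) × 0.405 = 72.2%

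| Recurrence / death / loss | All included | Known status | Gap (points) | Target A | Target B |
|---|---|---|---|---|---|
| 30 / 5 / 5% | 63.2% | 68.8% | 5.7 | 66.5% | 70.7% |
| 30 / 10 / 10% | 56.7% | 67.6% | 10.9 | 63.0% | 71.4% |
| 30 / 15 / 15% | 50.6% | 66.2% | 15.6 | 59.5% | 72.2% |

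Gaps are from unrounded values.

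**Direction.** In every row the known-status percentage lies above target A and below target B, so the sign of its error depends on the target. It also depends on why patients are missing. Take a true rate of 70%, no deaths and 10% lost:

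- loss independent of outcome: excluding the lost gives 0.630/(0.630 + 0.286) = 68.8%, too low;
- all the lost had relapsed: 0.70/0.90 = 77.8%, too high;
- all the lost were disease-free: 0.60/0.90 = 66.7%, too low.

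**Bound without a model.** If a fraction m is unresolved, the percentage moves by 100 × m points between calling all of them failures and all of them successes. With 40 patients, 4 unresolved and 25 of the other 36 disease-free, the choices are 25/40 = 62.5%, 25/36 = 69.4% and 29/40 = 72.5%.

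**The case against.** **An article may leave the denominator and missing-data rules to a fuller document.** This stands, and the missing rule alone would be no finding. The point here is narrower: the article does state a method, and that method does not suit the time-based outcome it also states.

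**Section 2.6 never names the MSI outcome.** True. That the outcome will be shown as a percentage is the natural reading of the text, not an explicit statement.

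**Death can be counted as failure.** This stands. It gives a well-defined proportion, which with complete follow-up equals the Kaplan-Meier estimate. Death is a choice of target; loss to follow-up is what a percentage cannot handle.

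**The registry is exploratory and has no test.** This limits the harm to a rate that is hard to interpret. It does not favour percentages, because Kaplan-Meier and cumulative-incidence estimates are equally descriptive.

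**Stronger readings that the documents do not support.** A reader might infer that dropping incomplete patients always overstates success; the direction check shows that it does not. A reader might quote a gap above 15 points; that appears only in the most extreme of three assumed scenarios. A reader might treat every amputation as an event competing with recurrence; Section 2.2 names it as an assigned control treatment, and then it is no follow-up event. A reader might extend the point to chronic rhinosinusitis (CRS) and sepsis; Section 2.4.2 gives those indications scores and other measures, with no recurrence-free endpoint.

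**Conclusion.** The point holds for the MSI one-year outcome. The stated method cannot use partial follow-up, so once patients die or are lost the disease-free rate is not uniquely defined. Under the assumed risks, two natural denominators differ by about 6 to 16 points. These figures rest on constant, independent hazards and on rates that are not in the article; with little death or loss the gap would be small. No general direction of bias can be claimed.

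Amputation is a related question of outcome definition. Nothing in the text prevents a control whose infected limb was removed from being counted as disease-free, which would blur a display by treatment received. The article does not say that this will be done.

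The change is worth making because the alternative is better and costs little. It does not call the registry's design or its descriptive aim into question.

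**What to change.** In Section 2.6, for the MSI one-year outcome only and by treatment group:

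1. Report a Kaplan-Meier estimate of recurrence-free survival at one year, with recurrence or death as the event and loss to follow-up censored, and a 95% confidence interval.
2. Report the cumulative incidence of recurrence, with death as a competing event and a 95% confidence interval.
3. Use the same time origin in both groups, or state plainly that the origins differ. The estimators do not repair that difference.
4. Report amputations that occur during follow-up separately. Show controls whose assigned treatment was amputation as their own category, not pooled as disease-free.
5. Give the denominator of any percentage that is kept.

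Keep simple summaries for baseline data and for the CRS and sepsis scores.

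**Cost.** No added patients or visits, and slightly more analysis work. The sponsor should confirm that the case report form captures dates of recurrence, death and last contact. Intervals will be wide, since about 75 phage-treated patients are spread over three indications. The rate may look less favourable than one based on completers only.
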